**Baseline descriptive data**

Demographic and descriptive data is collected using a baseline questionnaire.
Table 3 includes a summary of descriptive data from patient participants. Descriptive data from GP participants will include: i) age; ii) gender; iii) years qualified as a GP; iv) practice size and location; v) special clinical interests, and; vi) any additional musculoskeletal training. Descriptive data from physiotherapist participants will include: i) age; ii) gender; iii) years qualified as a physiotherapist; iv) grade and v) special clinical interests.

**Patient clinical outcomes**

Selected clinical outcome measures are recommended by Outcome Measures in Rheumatology (OMERACT), Osteoarthritis Research Society International (OARSI). These include pain, physical function, quality of life, global assessment of the target joint, and adverse events
^
76
^.
Table 3 provides the full list of clinical outcome measures and time points of assessment.

**
*Knee function.*
** Self-reported knee function will be assessed using the Knee Injury and Osteoarthritis Outcome Score Physical Function Short Form (KOOS-PS)
^
77
^. This 7-item measure of physical function is derived from the activities of daily living and sport/recreation subscales of the Knee Injury and Osteoarthritis Outcome Score (KOOS). The KOOS-PS has been shown to be valid and reliable for use in people with knee OA. Scores range from 0 to 100 (extreme problems to no problems)
^
77
^.

**
*Knee pain.*
** Knee pain will be measured by the nine item pain subscale of the KOOS. Questions on this subscale pertain to the previous 7 days. It is scored (0 to 100) and reported individually
^
78
^. This KOOS subscale is a valid, responsive and reliable measure that have been used extensively in knee OA and knee arthroscopy trials
^
79
^.

**
*Pain self-efficacy.*
** The 2-items on the shortened form of the Pain Self-Efficacy Scale Questionnaire (PSEQ-2) reflect confidence in one's ability to work and lead a normal life despite pain
^
80
^. Items are scored on a 7-point Likert scale from "Not at all confident" to "Completely confident", with scores ranging from 0 (no confidence) to 12 (maximal confidence to perform activity despite pain). PSEQ-2 is valid and reliable and considered responsive enough to be used in a research context to evaluate changes after an intervention for chronic musculoskeletal disorders
^
81
^.

**
*Fear-avoidance beliefs.*
** A modified version of the four-item fear avoidance beliefs about physical activity subscale (FABQ-PA) will be used
^
82
^. Participants will rate their beliefs about the activity from 0 (completely disagree) to 6 (completely agree) and scores range from 0 to 24. While not formally validated in the knee, other studies have used this modified version in people with knee pain
^
83,
84
^. The word “back” has been substituted with the word “knee,” and the physical activities examples have been substituted with “running, walking, kneeling, and driving.”

**
*Health related quality of life.*
** The EuroQol Five-Dimensional Questionnaire (EQ-5D-5L) measures across five dimensions (mobility, self-care, usual activities, pain/ discomfort and anxiety/depression). The response options range from no problems (1) to unable or extreme problems (5). Overall health status is rated on a visual analogue scale from 0 (worst imaginable health) to 100 (best imaginable health)
^
85
^. Validity and reliability has been demonstrated in people with knee osteoarthritis populations
^
86
^.

**
*Global rating of change.*
** Self-rated overall level of improvement in knee symptoms (pain and physical function) will be assessed. Participants will be asked to respond to the questions: ‘Overall, how has your knee pain changed since the start of the study?’ and ‘Overall, how has your knee function changed since the start of the study?’ using Likert scale (7-point) ranging from ‘much worse’ to ‘much better’.

**
*Satisfaction with care.*
** Participants will be asked to rate the “overall satisfaction with the care you received in this study” using a 7-point scale ranging from “extremely unsatisfied” to “extremely satisfied”

**
*Adherence to the exercise and physical activity plan.*
** Adherence to the exercise and physical activity plan agreed with the physiotherapists will be rated by the patient participant on an 11-point Numerical Rating Scale (0 = not at all and 10 = completely as instructed).

**
*Recovery expectations.*
** Expectation of recovery are assessed using a 7-point ordinal scale in response to the question “How much do you expect your knee problem to change in the next 6 months?” ranging from ‘completely recovered’ to ‘worse than ever’.

**
*Use of health care and co-interventions for knee pain.*
** A self-report checklist will record visits to health care providers (additional physiotherapy and GP consultations, other health professional or secondary care consultations), injection use, complementary therapies and imaging between baseline to 12 weeks and at 6-month follow-up using a customised questionnaire.

**
*Change in pain medication usage.*
** Self-report change in pain medication use from baseline to 12-week and 24 follow-up will be assessed with a 7-point Likert scale (much less to much more).

**
*Number of working days missed.*
** The number of work days (paid employment or unpaid work) missed due to the knee problem since baseline will be recorded.

**
*Adverse events.*
** Defined as any problem that participants believe was caused by the intervention (exercise or advice) and requiring them to seek treatment and/or lasted for two or more days. Adverse events reported to the research team by participating patients, GPs or physiotherapists will be recorded in an adverse events log. Follow-up questionnaire at 12 weeks and 6 months will specifically ask patients about adverse events by including an open probing question. All qualitative interviews conducted with participants will ask about adverse events.

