### Intervention for health care professional and patient participants

The KNEE-DEeP intervention (
Figure 2) is a complex intervention designed to improve the uptake of evidence-based care for early OA and DMTs, by targeting the behaviours of both HCPs and their patients
^
48
^. Evidence based care is informed by clinical practice guidelines and focuses on patient education, exercise and promoting self-management
^
11,
15,
26
^. The KNEE-DEeP intervention will aim to ensure patients receive evidence based management and consistent information at an early point in their care from both the GP and physiotherapist, thereby reducing unnecessary referral to secondary care and inappropriate imaging. GPs and physiotherapists will receive specific training to deliver the patient intervention and enhance their skills and confidence in managing patients with this type of knee pain. Content and design of the HCPs training session will draw on evidence from a range of chronic musculoskeletal conditions
^
64–
69
^. The content of the intervention aligning to the Template for Intervention Description and Replication (TIDieR) guidelines is summarised in
Table 2
^
70
^.

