### Outcomes

**Feasibility and implementation outcomes**

Data will be collect on implementation and feasibility outcomes to inform decisions about the need for further evaluation of the KNEE-DEeP intervention and a fully-powered trial. Proctor and colleagues framework on outcomes for implementation research was used to select a series of appropriate feasibility and implementation outcomes
^
71
^. Data will be collected on intervention feasibility, intervention acceptability, the feasibility and acceptability of study procedures, intervention fidelity, and preliminary efficacy. Quantitative data using self-report questionnaires and qualitative interview data from both HCPs and patients will be integrated to gain a comprehensive understanding of intervention delivery and implementation processes. Incorporating qualitative data collection is recommended given the capacity to this type of data to add depth to the interpretation of such feasibility study evaluations
^
72
^.
Table 1 illustrates the timing of quantitative and qualitative data collection.
Table 3 summarises all data collection from patient participants.

**Table 3. T3:** Summary of quantitative data collection from patient participants.

Domain	Measurement Tool	Baseline	12 weeks	24 weeks
*Descriptive data*				
Age, gender, self-report weight and height		X		
Education level		X		
Employment status and occupation		X		
Current pain medication use		X		
History of knee injury, kneeling occupation or previous surgery		X		
Symptom duration				
Other knee symptoms		X		
Other pain sites		X		
Comorbidities		X		
*Primary Clinical Outcome Measures*				
Knee function	KOOS-PS	X	X	X
*Secondary Clinical Outcome Measures*				
Knee pain	KOOS pain subscale	X	X	X
Pain self-efficacy	PSEQ-2	X	X	X
Fear avoidance beliefs	FABQ	X	X	X
Health related quality of life	5Q-5D-5L	X	X	X
Satisfaction with care	Self-rated on 7-point ordinal scale for GP and physiotherapy care		X	
Global rating of change	Self-rated on 7-point ordinal scale		X	X
Number of working days missed	Self-reported			
*Additional Measure*s				
Recovery Expectations	5-point ordinal scale	X		
Adherence to the exercise and physical activity plan	Self-rated on 11-point NRS		X	
Data on healthcare utilisation	Self-reported use of health services and co-interventions		X	X
Change in pain medication use	Self-rated on 7-point Likert scale		X	X
Intervention acceptability	TFA Questionnaire		X	
Harms	Self-report of adverse events		X	X

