The Trial Management Committee (TMC) will oversee the day to day running of the trial and have responsibility for data monitoring. This committee will comprise of the PI and five grant collaborators. An independent Trial Steering Committee (TSC) will oversee the study. This includes an independent chairperson, two other independent members and a lay representative. The PI ([name]), and another member ([name]) of the TMC will attend the TSC meetings and report progress. The TSC meetings will be scheduled approximately every three months, and it is anticipated the committee will meet five times over the course of the study. Safety considerations associated with this trial are minimal because education and exercise for knee pain are associated with minimal adverse events. Any serious adverse events will be recorded and reported to both the ethics committee and the TSC. The committee will have responsibility for making decisions about modifying or discontinuing the intervention in response to any reported or potential harms. As this is a low risk trial, the Steering Committee will also act as the Independent Data Monitoring Committee (IDMC).

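### A problem counts as an adverse event only if participants believe the exercise or advice caused it, so unattributed problems drop out of the harms outcome

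*Protocol article*

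**What the plan says.** The adverse events paragraph under Patient clinical outcomes has two conditions. The first is attribution: "Defined as any problem that participants believe was caused by the intervention (exercise or advice) and requiring them to seek treatment". The second is a threshold of consequence or duration: "and requiring them to seek treatment and/or lasted for two or more days".

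Collection is described in the same paragraph. On the log: "Adverse events reported to the research team by participating patients, GPs or physiotherapists will be recorded in an adverse events log". The follow-up questionnaires at 12 weeks and 6 months "will specifically ask patients about adverse events by including an open probing question", and the qualitative interviews also ask about adverse events. Table 3 gives the harms measure as "Self-report of adverse events".

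Under Data management plan and study oversight, serious events get one sentence on recording: "Any serious adverse events will be recorded and reported to both the ethics committee and the TSC". It carries no attribution condition. The steering committee, which also acts as the independent data monitoring committee, is responsible for "making decisions about modifying or discontinuing the intervention in response to any reported or potential harms".

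The intervention section states that the pathway aims at consistent early management, "thereby reducing unnecessary referral to secondary care and inappropriate imaging".

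**The concern.** A harms outcome normally separates two questions: did something untoward happen, and was it related to the intervention? Here the second question is built into the first. One belief decides both whether an event exists and whether it is related, and the article describes no separate judgement of relatedness.

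This fits the intervention poorly. Part of the pathway's intended effect is that some imaging and referral does not happen. Harm by that route, for instance a later diagnosis than would otherwise have been made, comes from something not done. The article does not name this example; it is an illustration drawn from the stated aim. Some patients would blame the advice and be counted, and others would not.

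At stake are the reading of a short or empty adverse event list in a study with no control group, part of the information reaching the steering committee, and the harms definition carried into a later trial.

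**Working it through.** The article states no event rate, so there is no figure to reproduce. The main check is textual.

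**Step 1. Apply the definition.** Classify any problem by threshold (treated or lasting at least two days) and by attribution (believed due to the exercise or advice):

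| | Attributed | Not attributed |
|---|---|---|
| Threshold met | Adverse event | Not an adverse event |
| Threshold not met | Not an adverse event | Not an adverse event |

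The point is the top right cell. The duration clause is an alternative to seeking treatment, not an alternative to attribution, so it does not rescue those problems.

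**Step 2. Look for a route around the filter.** The log, the questionnaires, the interviews and the Table 3 self-report all collect adverse events, which is the defined term. Letting GPs and physiotherapists report widens who may report, not what counts. If the word participants is read to include clinicians, belief in causation is still required.

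**Step 3. Serious events.** The oversight section attaches no attribution condition and gives no definition. An unattributed serious event may be recorded under that sentence, or the general definition may be taken to apply. The text does not settle which.

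**Step 4. Other data.** Outside the harms outcome the article collects health-care use and imaging, global change in pain and function, and change in pain medication at 12 weeks and 6 months, as well as KOOS pain. None is conditioned on attribution, and none is classed as a harm. They could reveal some top-right-cell problems, but only if someone looks.

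**Step 5. Illustrative size.** The input is n = 36, the patient recruitment target. Zero observed events, no loss to follow-up and the attributed fraction f are assumptions.

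- Complete capture: solve (1 − p)^36 = 0.05, so p = 1 − 0.05^(1/36) = 0.0798, or 8.0%.
- Only a fraction f of true events attributed: solve (1 − f·p)^36 = 0.05, so p = 0.0798 / f.

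| f (assumed) | Upper bound for the true rate |
|---|---|
| 1.00 | 8.0% |
| 0.90 | 8.9% |
| 0.75 | 10.6% |
| 0.50 | 16.0% |
| 0.25 | 31.9% |

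The article gives no basis for choosing f. The table shows direction and form only.

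**The case against.** The case against is substantial.

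- *Serious events.* A reader might infer that these inherit the filter. The article does not say so: its sentence covers any serious adverse event without condition, and a condensed article may leave the definition to the full protocol. This stands. All that remains is that the two sections should be made explicit about each other.
- *Steering committee.* A reader might infer that it decides from the adverse event log alone. Its remit covers reported or potential harms, which is wider. This stands; the filtered log is one input.
- *Delayed diagnosis.* A reader might infer that this is excluded by definition. It is not. Being told that a scan or referral is unnecessary is advice, and a patient who blames it is counted. Exclusion depends on the attribution made. The aim is also limited to unnecessary referral and inappropriate imaging. GPs are trained to screen for serious disease, and a physiotherapist reassesses the patient within two weeks. The example is possible, not established as likely.
- *Whose belief.* GPs and physiotherapists are also study participants, so the belief might be theirs. The words about seeking treatment favour the patient. On either reading a belief in causation is needed.
- *Existing data.* Worsening and extra care are visible in other outcomes. This is true and softens the consequence, but they do not enter the harms count.
- *Scale.* No objective concerns safety, the study is small and considered low risk, and even perfect capture leaves an 8.0% bound at zero events. This limits the seriousness without repairing the definition.
- *Noise.* Wider recording will list ordinary flare-ups, which are hard to interpret without a control arm. This is a real cost, and a reason to keep attribution as a recorded item.

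**Conclusion.** The point holds in limited form. As written, problems that meet the treatment or duration threshold but are not attributed to the exercise or advice are left out of the harms outcome, so harms can be under-counted. This rests on the wording of the definition and on every listed collection route using the same term. It does not depend on any assumed rate.

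Whether the condition extends to serious adverse events is unresolved. The size of the under-count is unknown. The 8.0% bound assumes zero events among 36 fully followed patients, and a figure such as 16.0% needs an assumed attributed fraction of one half, so neither estimates anything about this study. A reader should not conclude that serious events will go unrecorded or that the committee will be blind to harm.

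The weakness is moderate in a low-risk, single-arm feasibility study. It is worth correcting because the correction is simple and the definition may be reused in a later trial.

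**What to change.** For data still to be collected:

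1. Record any new or worsened knee or exercise-related problem that led to treatment or persisted for at least two days, whoever reports it and whatever its believed cause.
2. Collect perceived attribution as a separate item on the questionnaire and in the log.
3. Report all events beside attributed events. The second count keeps the present definition.
4. State in the oversight section that serious adverse events are recorded and reported regardless of attribution.

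The Trial status section says that patient recruitment began in June 2024, was continuing when the article was written, and that completion was due in June 2025. For patients already followed up, report the attribution-based definition as a limitation. Review their health-care-use and global-change responses for problems that were not attributed, labelling what is found as retrospective. Carry the revised definition into any later trial.

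The direct cost is a reworded item and a longer log. More unrelated problems and ordinary flare-ups will be listed, and two definitions will apply across the study, so counts before and after the change should be shown separately. The change also has to go through the article's own route for deviations: the ethics board, the registry and the results paper.

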### Data collection and analysis plan

**Data analysis plan**

As this is a feasibility study, the main focus will be on feasibility and implementation outcomes to inform decisions about further evaluation and a fully-powered trial. For the process evaluation, insights into intervention feasibility, acceptability and the feasibility of study procedures will be identified from coded interview transcripts and survey results will be analysed using descriptive statistics. These findings will be integrated by accompanying quantitative data with qualitative findings in a joint display
^
87
^. A more detailed description of quantitative and qualitative analysis is included below.

**Quantitative data collection and analysis**

Data relating to study procedures (recruitment, retention etc) will be collected throughout. Participants will be invited to complete the baseline and follow-up questionnaires via an online link to Microsoft (MS) Forms. Data from MS Forms will be stored electronically on UL’s secure OneDrive cloud storage, exported to Microsoft Excel. Participants will also have the option of completing paper questionnaires, if this is their preference. Data from paper based questionnaires will be transferred by a researcher to Microsoft Excel. Demographic data from GPs and physiotherapists will be collected following study enrolment at the training workshops by paper questionnaire.

Follow-up questionnaires will be sent to patient participant at 12 weeks and 6 months. For those who do not respond, at least one reminder will be sent, via email or by post. For those who do not respond to the reminder, a telephone follow-up will be used to contact participants. Participating GPs and physiotherapists will complete a follow-up questionnaire at the conclusion of recruitment and intervention delivery.

Participants’ characteristics and implementation outcomes will be described using descriptive statistics such as means, standard deviations and ranges for quantitative variables, and counts and proportions for categorical variables. Descriptive statistics will also be used to measure change in outcome measures from baseline to 12 weeks and 6-month time-points and results will be treated as exploratory. Means and confidence intervals of the KOOS-PS will be calculated in order to inform the sample size calculation for a future definitive RCT.

**Qualitative data collection and data analysis**

**
*Patient interviews.*
** Semi-structured interviews will be conducted by a female researcher with a background in qualitative methods, and who is not directly involved in the study. Interviews will be by telephone or online, depending on participant preference. Ten to 12 of the patient participants will be purposively recruited with the aim of interviewing a diverse sample, based on clinical characteristics, and participants from a range of participating GP practices. Interviews will be conducted within a month of receipt of the ‘best practice’ physiotherapy intervention, where possible, and last for approximately thirty minutes. The interview topic guide will focus on acceptability and feasibility of the study intervention and procedures, as outlined above, and also include : 1) patients’ experience of receiving the intervention from the GP and the physiotherapist; 2) perception of its benefits, 3) barriers to engagement with aspects of the intervention; 4) suggested improvements on aspects of the intervention or study design.

**
*HCP interviews.*
** Qualitative data will be collected from six to eight GPs on conclusion of the patient recruitment phase. Data collection will be via a combination of one to one interviews and a small focus group moderated by clinician researcher not directly involved with the study. The dynamics of the focus group discussion should help promote debate and a range of views about the KNEE-DEeP study intervention
^
88
^, yielding rich data on acceptability and feasibility. Interviews will take place either in-person or online, depending on participant preference
*.* Five physiotherapists who delivered the physiotherapy intervention will also be interviewed. The topic guides will explore the experiences of those HCPs participating in the study and issues of implementation relating to acceptability, feasibility, fidelity, as outlined in the outcome section above.

Transcription will be undertaken in parallel to data collection. Transcripts will be de-identified and offered to participants for approval or amendment. The NVivo qualitative analysis software programme
^
89
^ will be used to support data analysis and enable an audit trail of analysis decisions. Open coding of the data set will be undertaken before using thematic analysis
^
90
^. The research team will code the data, with peer coding of select transcripts, to enable cross-coding comparisons, before identifying themes and sub-themes. The wider research team including the PPI group, will contribute to interpretation the findings.

